##### Subjective appraisal of the program

The subjective appraisal of Lenio will be assessed using the German version of the Client Satisfactory Questionnaire (CSQ-8; German acronym is ZUF-8). According to the literature, the psychometrics of the CSQ-8 are high, with internal consistency ranging from Cronbach’s α = 0.87 to 0.93 [24, 28]. Satisfaction can be assessed on a 4-point rating scale (“excellent,” “good,” “less good,” “bad”). A high score indicates high satisfaction. The wording has been adapted by replacing “psychotherapy” with “self-help intervention Lenio.” Additional subjective data will be assessed by 12 further questions on the quality, utility, and applicability of Lenio in both open and closed response format (see Table 3).

**Table 3 Tab3:** Subjective quality, utility, and application of Lenio

1. How regularly did you use the Internet-based self-help program Lenio?	◦ **Daily** **◦ 5–6 times per week** **◦ 3–4 times per week** **◦ 1–2 times per week** **◦ Less than once a week** **◦ Less than 5 times in the whole period** **◦ I have only used Lenio once**
2. Which topics were you able to complete in Lenio?	**◦ Introduction** **◦ Basic needs** **◦ Attentional control and mindfulness** **◦ Sleep** **◦ Self-worth** **◦ Modifying thoughts** **◦ Relapse prevention** **◦ Social competence** **◦ ACT** **◦ Incorporating positive activities**
3. I think Lenio is suitable for self-application	**◦ Applies** **◦ Rather applies** **◦ Rather not applicable** **◦ Not applicable** **◦ No answer possible**
4. I found Lenio to be helpful	**◦ Applies** **◦ Rather applies** **◦ Rather not applicable** **◦ Not applicable** **◦ No answer possible**
5. I think the instructions were written comprehensibly	**◦ Applies** **◦ Rather applies** **◦ Rather not applicable** **◦ Not applicable** **◦ No answer possible**
6. I was able to use Lenio regularly over the past weeks	**◦ Applies** **◦ Rather applies** **◦ Rather not applicable** **◦ Not applicable** **◦ No answer possible**
7. I had to push myself to use Lenio	**◦ Applies** **◦ Rather applies** **◦ Rather not applicable** **◦ Not applicable** **◦ No answer possible**
8. I feel that Lenio has reduced my chronic pain	**◦ Applies** **◦ Rather applies** **◦ Rather not applicable** **◦ Not applicable** **◦ No answer possible**
9. I feel that Lenio has reduced my emotional problems	**◦ Applies** **◦ Rather applies** **◦ Rather not applicable** **◦ Not applicable** **◦ No answer possible**
10. What would help you to better integrate Lenio into your everyday life?	
11.What did you like about Lenio?	
12. Do you have any suggestions for improvement?	

The answers to the seven closed questions will be assessed on a four-point Likert scale (“not applicable” to “completely true”). The open questions ask for positive and negative feedback on Lenio and will ask for improvement suggestions.

In addition, the participants will be asked to indicate how regularly Lenio was used during the intervention period. Subjective data will be assessed at post intervention and follow-up.

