**Discussion:**

Lenio is one of the first Internet-based interventions to reduce chronic pain and depression that will be empirically evaluated. Internet-based interventions could offer a promising alternative to conventional face-to-face psychotherapy in the treatment of chronic pain patients. The primary objective of the current study is to add essential insight into the feasibility, effectiveness, and acceptance of Internet-based interventions for people with chronic pain and depressive symptoms.

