### Objectives {7}

The aim of the current research project is to investigate the feasibility, effectiveness, and acceptance of the Internet-based self-help intervention Lenio in combination with the smartphone app COGITO in an RCT. As the primary objective, a significant reduction in pain impairment (mean value of impairment in daily life, leisure time, and work; primary outcome) as measured by the German Pain Questionnaire (German acronym: DSF) in the intervention group compared to a waitlist and an active control group is expected. Furthermore, we also assume that depressive symptoms, as well as pain-related cognitive biases (e.g., catastrophizing, fear-avoidance beliefs), will be significantly reduced in the intervention group compared to the two control groups. Hence, the treatment of a highly prevalent condition could be improved.

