### Participant timeline {13}

After giving informed consent, sociodemographic and psychopathological data will be assessed. At the end of baseline, individuals will be randomized equally to one of the three conditions. Randomization will be conducted automatically in Qualtrics®, preventing influence by third parties {16a}. At post-intervention and follow-up, psychopathological data, subjective evaluation, and side effects will be examined. For participating in each of the three online surveys (baseline, post, follow-up), participants will receive €10 Amazon® vouchers (as much as €30 total) as an incentive.

Instructions after baseline will be delivered via e-mail. The intervention group will receive their login details for Lenio and COGITO. One week later, individuals in the intervention group who do not log into Lenio will receive a reminder, including an overview of the program. Adherence will be further enhanced by sending e-mails that include descriptions (including tips) of specific modules. The active control group will receive instructions and an MCT & More download link for Android and IOS. Both the active control and the waitlist control group will receive log-in details for Lenio after completion of the follow-up survey 16 weeks after baseline.

Links to the post and follow-up assessments will be sent by automatically triggered e-mails. If participants will have not participated in a particular survey, they will receive a maximum of two e-mail reminders at intervals of 1 week. (The first e-mail reminder will be automated. However, the second reminder will be a personal message from the principal study investigator) {18b} (Table 1).

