### Sample size {14}

The sample size calculation was conducted using G*Power®. Given that Miegel and colleagues [39] examining the effect of an unguided Internet-based interventions for depression on chronic pain patients found small to moderate effects, a moderate effect in the current study can be expected [39]. For analysis of covariance, the software yielded a required sample size of 246 with an expected effect size of η_p_^2^ = 0.06 (moderate effect), an alpha of 0.05 (two-sided), and a power of 0.95. We expect a drop-out rate of 25%. Hence, we aim to recruit 300 participants in total, with 100 participants per condition.

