### Methods for additional analyses (e.g., subgroup analyses) {20b}

Explorative moderation analysis will be conducted using the SPSS® macro PROCESS [20] to identify potential moderators for treatment success (all types of baseline variables are being considered in this type of analysis). Furthermore, subjective evaluation of the intervention will be done descriptively by presenting the frequency of positive ratings as well as means and standard deviations.

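### Programme use and acceptance rest on self-report by survey responders, while Lenio log-in status, already tracked in the intervention arm, has no planned summary

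*Protocol article*

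**What the plan says.** Under Objectives {7}, the trial sets out to "investigate the feasibility, effectiveness, and acceptance of the Internet-based self-help intervention Lenio in combination with the smartphone app COGITO in an RCT". The Discussion paragraph of the Abstract goes further: "The primary objective of the current study is to add essential insight into the feasibility, effectiveness, and acceptance of Internet-based interventions". Objectives {7} itself reserves the term primary objective for pain impairment, so feasibility and acceptance are declared aims but not the tested primary endpoint.

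The section on subjective appraisal of the program describes the data. Satisfaction is measured with the ZUF-8, reworded to refer to Lenio. Twelve further questions (Table 3) cover quality, utility and application, including how often Lenio was used and which topics were completed. The same section adds that "the participants will be asked to indicate how regularly Lenio was used during the intervention period", and on timing: "Subjective data will be assessed at post intervention and follow-up".

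The analysis is in section {20b}: "subjective evaluation of the intervention will be done descriptively by presenting the frequency of positive ratings as well as means and standard deviations". Multiple imputation is mentioned in {20c} for the intention-to-treat analyses. Nothing extends it to these descriptive summaries, and no denominator is given for them.

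Three other places bear on the point:
- Sample size {14} expects 25% drop-out and plans 100 participants per condition.
- Participant timeline {13} says that, after one week, "individuals in the intervention group who do not log into Lenio will receive a reminder".
- Section {20c} limits the per-protocol sample to people who completed the post-assessment and used both Lenio and COGITO at least once. It does not say where the evidence of use comes from.

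**The concern.** Someone who stops using an unguided program, or never starts, is plausibly also someone who does not return the post survey. If use and ratings are known only for people who answer, the picture is conditional on staying in the study. The Background section on Internet-based psychological interventions names adherence as the chief weakness of unguided programs, so use is a quantity this trial should measure with as little selection as possible.

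The use question adds a second pull in the same direction. Its lowest category is a single use. A responder who never opened Lenio must skip the item or choose a category that merges non-use with light use.

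The described items also concern Lenio only, whereas the tested intervention is Lenio together with COGITO and the per-protocol sample depends on use of both. What is at stake is the credibility of the answer on feasibility and acceptance, and whether the per-protocol sample can be reproduced.

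**Working it through.** **Inputs from the protocol article.** Intervention arm n = 100 and expected drop-out d = 0.25 (Sample size {14}). The 25% is an overall expectation, not one for the Lenio arm. The plan's computed sample size of 246 reproduces closely: a noncentral F calculation with f² = 0.06/0.94, 3 groups, 2 numerator degrees of freedom and one covariate gives 245. That figure plays no part here; only d and n do.

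**Assumed inputs.** The article gives neither p, the proportion of responders reporting regular use or a positive rating, nor q, the same proportion among non-responders had they been observed. Both are varied below.

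**Responders.** 100 × (1 − 0.25) = 75. With p = 80%, 0.80 × 75 = 60 participants are positive.

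**Formula.** Rate among all randomised: r = (1 − d)p + dq. The responder figure is p, so its excess is p − r = d(p − q) = 0.25 × (p − q).

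**Results at p = 80%:**

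| q assumed | r = 0.75 × 0.80 + 0.25 × q | Excess of the responder figure |
|---|---|---|
| 0% | 60% | +20 points |
| 40% | 70% | +10 points |
| 80% | 80% | 0 |
| 100% | 85% | −5 points |

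**Other values of p, with q = 0.** At p = 60% the excess is 0.25 × 60 = 15 points; at p = 90% it is 0.25 × 90 = 22.5 points.

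**Other drop-out in the Lenio arm (assumed), p = 80%, q = 0.** At d = 35% the excess is 0.35 × 80 = 28 points.

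**Use item.** The missing category for non-use affects responders too, so it can raise p even without drop-out. The article gives nothing from which to size this.

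**Availability of a better source.** A reminder triggered by not having logged in presupposes that log-in status is known for each intervention participant at one week, whether or not a later survey is returned. The Lenio description also says that the last page visited is saved, but as a way to resume, so it does not establish that a usage history is kept. No analysis of either is described.

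**The case against.** The strongest reply is that a journal article condenses a longer document, and that denominators, handling of non-responders and usage metrics are often left to it. That holds for the missing denominator rule: a reader might infer that the plan prescribes a responders-only analysis, but the text states no such rule. It holds less well for the choice of measure, because the article does describe how use is to be measured, by self-report, and that choice can be improved at little cost.

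Several stronger readings are tempting and are not supported:
- That log-in data exist for everyone. The text implies Lenio log-in status for the intervention arm only; both control groups receive Lenio after the 16-week follow-up. Retention of the records and their linkage to the surveys are not stated.
- That use and acceptance are certainly overstated. This needs q below p. Vouchers and survey reminders are offered whatever the level of use, which weakens the link between non-use and non-response.
- That feasibility is formally judged from the Table 3 item. No measure is assigned to feasibility.
- That COGITO use is not recorded. The per-protocol definition requires it, so a source may exist; it is simply not named.

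It is also fair to say that someone who gave no satisfaction rating has none, so counting non-responders as not positive is a worst case and not a neutral correction. The ZUF-8 is an established scale, and its use is not in question.

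**Conclusion.** The point holds as a worthwhile and inexpensive improvement to how use and acceptance are measured and reported. It does not touch the primary comparison of pain impairment.

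The described measures depend on returning a survey, about a quarter of participants are expected not to, and the use item cannot record non-use as such. Reported use is likely to be too high. At an assumed 80% among responders, the excess runs from 0 to 20 points as the rate among non-responders falls from 80% to 0, with a 5-point understatement if all non-responders were positive. The 20-point end is a bound that requires no non-responder to be positive; it is not an estimate. All of these figures assume that the overall 25% drop-out applies to the Lenio arm.

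**What to change.** 1. Make system records the main measure of Lenio use for all participants randomised to the intervention arm: ever logged in and, where the system kept them, modules reached and weeks with a log-in. Keep the self-reported frequency as supportive.
2. Beside every frequency of positive ratings, give the number responding out of all randomised to the arm. Show the figure with all randomised as denominator only as a lower-bound sensitivity.
3. In {20c}, name the data source for use of Lenio and of COGITO in the per-protocol definition, or state that COGITO use is not recorded.

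New survey items are not a useful remedy, because the article reports that recruitment is completed.

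The cost is one export, one extra column in the tables and one sentence in the per-protocol definition. The use figures may become less favourable. The first step depends on the log-in records having been kept. If linking them to survey data relies on the e-mail addresses (an assumption), it must be done before those addresses are deleted at the end of the study. Where a withdrawn participant's data have been deleted, the person should remain in the count of those randomised, with use shown as unknown.

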## Statistical methods

### Statistical methods for primary and secondary outcomes {20a}

All analyses will be conducted using IBM SPSS Statistics® 27. The data will be exported from Qualtrics® into SPSS® and initially stored on a secure server and later a password-protected computer. The security of data transmission via the Internet is also guaranteed by SSL encryption. Data will be analyzed using analysis of covariance (ANCOVAs), with between-group differences over time (pre-intervention to post-intervention) as the within-group factor and different conditions as the between-group factor. Baseline scores will serve as covariates, group allocation as the independent variable, and post- and follow-up scores of primary and secondary measures as dependent variables. Group differences at baseline will be assessed using independent t-tests for continuous variables. Partial eta square will be calculated as effect size.

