### Trial design {8}

The self-guided Internet-based intervention Lenio will be evaluated in the framework of a randomized controlled trial (RCT). Participants will be randomly allocated (ratio 1:1:1) to one of three conditions: (1) intervention group (direct access to the Internet-based intervention Lenio and the smartphone app COGITO), (2) waitlist control group, or (3) active control group (access to a transdiagnostic smartphone app named MCT & More).

The waitlist control will show the effect of the intervention against no treatment, while the active control will show the effect of the intervention versus an Internet-based intervention addressing psychological problems but not chronic pain {6b}.

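### The primary analysis is described as two incompatible models in consecutive sentences, leaving room for a covariate-free pre/post test beside the intended ANCOVA

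*Protocol article*

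**What the plan says.** All statements are in the protocol article.

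- **Statistical methods {20a}, first description.** ANCOVAs "with between-group differences over time (pre-intervention to post-intervention) as the within-group factor and different conditions as the between-group factor". This is the layout of a pre/post repeated-measures analysis, and it stops at post-intervention.
- **Statistical methods {20a}, next sentence.** "Baseline scores will serve as covariates, group allocation as the independent variable, and post- and follow-up scores of primary and secondary measures as dependent variables". This is a baseline-adjusted ANCOVA with no within-subject factor, and it adds follow-up.
- **Sample size {14}.** "For analysis of covariance, the software yielded a required sample size of 246", for a partial eta squared of 0.06, with "an alpha of 0.05 (two-sided), and a power of 0.95". Expected drop-out is 25% and the target is 300, 100 per condition.
- **Trial design {8}.** "Participants will be randomly allocated (ratio 1:1:1) to one of three conditions".
- **Abstract, Methods.** The primary outcome is the reduction in DSF pain impairment at the post-assessment, that is, after 8 weeks.

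No section says which of the two descriptions governs.

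**The concern.** The two sentences give the pre score different roles. In a pre/post repeated-measures model it is half of the outcome, and the treatment effect is the group-by-time interaction, which for two time points is a comparison of change scores. In the ANCOVA it is a regressor, and the treatment effect is the adjusted group difference at post. The Abstract's wording of a reduction at the post-assessment fits either reading.

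The two analyses use the same data but give different F values, different partial eta squared values and different power. If both can be defended from the text, the choice can be made after the outcome data are seen. This is not detail left to a fuller document: the article states the model, and states it two ways.

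**Working it through.** **Inputs.** From the document: three groups, 1:1:1; partial eta squared 0.06; alpha 0.05; power 0.95; required N 246; target 300 with 25% loss. Assumed, because the document gives no value: pre-post correlation ρ of 0.3, 0.5 or 0.7; equal variances at pre and post; and, in the simulations, equal means in the two control arms.

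**Step 1: reproduce 246.**
- f² = 0.06 / 0.94 = 0.0638, so f = 0.2526.
- ANCOVA F test with 2 numerator df, N − 4 denominator df (three groups, one covariate) and noncentrality λ = f² × N.
- The smallest N with power 0.95 is 245. Equal groups of 82 make it 246, with power 0.951. The stated figure is reproduced.

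**Step 2: does 246 exclude the repeated-measures reading?** With the usual repeated-measures definition of f, the group-by-time interaction needs 88, 64 and 40 at ρ = 0.3, 0.5 and 0.7. If 0.06 is instead read as an SPSS-type partial eta squared for the interaction, it needs about 245 to 248. So the number alone does not decide; the words of the sample size section do.

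**Step 3: apply both sentences literally (pre as level and as covariate).**
- Group by time: regress post − pre on group and pre. Subtracting pre changes only the coefficient of pre; the group coefficients and residuals are those of the ANCOVA, so F is the same.
- Group main effect: regress (pre + post)/2 on group and pre. The group coefficients and residuals are both halved, so F is again the same.
- One simulated dataset (82 per group, ρ = 0.5): ANCOVA F = 19.49, group by time F = 19.49, group main effect F = 19.49. The group-by-time test without the covariate gives F = 16.49.

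**Step 4: what the covariate-free group-by-time test costs.**
- Change-score variance: 2(1 − ρ)σ². ANCOVA residual variance: (1 − ρ²)σ². Ratio: 2/(1 + ρ).
- For the same raw effect, f² for the change score = 0.0638 × (1 + ρ)/2.
- At 300 × 0.75 = 225 (75 per arm), ANCOVA has λ = 0.0638 × 225 = 14.36 and power 0.93.

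| ρ | variance ratio | f² (change) | λ at 225 | power at 225, formula | power at 225, simulated | verdicts differ |
|---|---|---|---|---|---|---|
| 0.3 | 1.54 | 0.0415 | 9.34 | 0.78 | about 77% | about 17% |
| 0.5 | 1.33 | 0.0479 | 10.77 | 0.84 | about 85% | about 10% |
| 0.7 | 1.18 | 0.0543 | 12.21 | 0.88 | about 88% | about 6% |

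The last column is the share of simulated trials in which one test is significant at 0.05 and the other is not. Repeated simulation runs differ by about one percentage point.

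**Step 5: separate this from drop-out.** The fall from 95% to 93% for ANCOVA comes from having 225 rather than 246 analysed, not from the model wording. At 246 the comparison is 95% for ANCOVA against 82%, 87% and 91% for the covariate-free test, which would need about 376, 326 and 288 for 95%.

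**The case against.** The strongest reply is that the governing model can be identified. The section names ANCOVA, its second sentence assigns every role, and the sample size section names the same method. One garbled clause points elsewhere. This stands in large part: the document leans clearly to the baseline-adjusted ANCOVA. It does not remove the clause, which describes a recognisable and common analysis.

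A fuller protocol or analysis plan may also state the model. That is possible, but the article's own two sentences would still conflict.

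Three stronger readings are tempting, and the document does not support them.

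- **That the primary result depends on which row of the output is read.** Step 3 rules this out whenever baseline is in the model, because all between-group rows then give the same F.
- **That power could collapse because someone tests the unadjusted group effect averaged over pre and post.** This requires ignoring the explicit sentence on covariates and choosing a test the text never suggests; even the faulty clause speaks of differences over time.
- **That only the ANCOVA can produce 246.** Step 2 shows that an SPSS-type effect size gives nearly the same number for the interaction. The tie to ANCOVA rests on the wording.

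**Conclusion.** The contradiction is in the text and concerns the primary analysis, so it should be corrected. Its consequence is moderate. Taken together, the two sentences give a redundant model but an unbiased group comparison. What remains open is a choice between the ANCOVA and a covariate-free pre/post group-by-time test. At 75 per arm that choice is worth about 93% against 77% to 88% power, and it changes the verdict in about 6% to 17% of simulated trials.

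These figures rest on the planned effect size, equal control arms, equal variances at pre and post, and an assumed correlation of 0.3 to 0.7. The loss is larger when the correlation is lower.

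**What to change.** Delete the within/between-factor clause and state one model, for example: Primary analysis is an ANCOVA of DSF pain impairment at week 8 on group, with baseline pain impairment as covariate; the primary test is the adjusted group effect. The week-16 score is analysed by the same model as a secondary time point.

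The cost is one sentence. No new data are needed, the required 246 is unchanged, and the text then agrees with the sample size section and the Abstract. Recruitment is complete and first data were analysed for the March 2022 interim report, so the change should be dated and made before the final outcome analysis.

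The sentence does not settle how the comparisons with the two control groups combine into the primary conclusion; that is a separate question.

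### The stated 95% power belongs to a three-group F test, not to the primary objective of superiority over both waitlist and active control

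*Protocol article*

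**What the plan says.** Objectives {7} states the primary objective as a significant reduction in DSF pain impairment "in the intervention group compared to a waitlist and an active control group is expected". Trial design {8} gives each control its own question. One comparison is with untreated participants: "The waitlist control will show the effect of the intervention against no treatment". The other is with users of a psychological app that has no pain content, and is a separate question from the first. The Discussion repeats the expectation and again names both controls.

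Statistical methods {20a} specifies ANCOVA: "Baseline scores will serve as covariates, group allocation as the independent variable", with post and follow-up scores as dependent variables. It adds: "Partial eta square will be calculated as effect size". It names no comparison between particular arms.

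Sample size {14} contains a single calculation: "For analysis of covariance, the software yielded a required sample size of 246", for a partial eta squared of "0.06 (moderate effect), an alpha of 0.05 (two-sided), and a power of 0.95". The section then assumes 25% drop-out and sets a target of 300, or 100 per arm.

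**The concern.** The objective makes two directional statements, each about Lenio against a named comparator. The sample size rests on a test of whether three means are all equal. That F test has no direction and no comparator. It can be significant because Lenio beats both controls, because Lenio and the app both beat the waitlist, or because the app alone differs. Partial eta squared does not separate these cases, since it has no sign, no reference arm and no unit on the pain scale.

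Two things are at stake. A significant group factor could be read as meeting the primary objective when it does not. And a reader would take 95% as the chance of showing the stated objective when the true figure is lower, above all against the active control. The article itself makes a small gap between Lenio and the app conceivable. MCT & More is described as a pilot version of COGITO with a similar design, and the Introduction reports that a pilot version of COGITO reduced depressive symptoms in regular users. That evidence concerns depression, not pain impairment.

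**Working it through.** **Inputs from Sample size {14}:** partial eta squared 0.06, two-sided alpha 0.05, power 0.95, required N 246 (82 per arm), drop-out 25%, target 300. **From Trial design {8}:** three arms, 1:1:1. **Assumption:** the pattern of the three means, which the article does not give, so a range is shown.

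**Step 1: reproduce 246.** f = √(0.06/0.94) = 0.2526. With three groups, one covariate, 2 numerator df, N − 4 denominator df and noncentrality N·f², the smallest N reaching 95% is 245. That becomes 246 in equal arms, with power 95.1%. Alternatives do not match: a 1-df test at the same f needs 206, and f = 0.25 gives 251 (2 df) or 210 (1 df). The figure is therefore that of the three-group F test.

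**Step 2: what the F test cannot distinguish.** Its power depends on the means only through f. In units of the residual SD, with means in the order Lenio, app, waitlist:

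- Equal controls (d, 0, 0): f² = 2d²/9, so d = 0.536.
- App midway (d, d/2, 0): f² = d²/6, so d = 0.619 against waitlist and 0.309 against the app.
- App equal to Lenio (d, d, 0): f² = 2d²/9, so d = 0.536 against waitlist and 0 against the app.

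All three have the same omnibus power: 95.1% at N = 246 and 93.1% at N = 225 (300 × 0.75). In the third pattern Lenio has no advantage over the app at all.

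**Step 3: power for the contrasts.** Each contrast uses a noncentral t with noncentrality d/√(2/n) and N − 4 df. For example, with equal controls at n = 82, 0.536 × √41 = 3.43, which gives 92.8%. Joint power comes from 400,000 simulated trials in which both contrasts share the Lenio arm and a pooled residual SD, with two-sided 0.05 for each.

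Each cell shows power against waitlist / against the app / against both:

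| Pattern (same f) | 82 per arm | 75 per arm | 100 per arm |
|---|---|---|---|
| Controls equal | 93 / 93 / 88% | 90 / 90 / 84% | 97 / 97 / 94% |
| App a quarter of the way to Lenio | 97 / 81 / 80% | 95 / 78 / 76% | 99 / 88 / 88% |
| App midway | 98 / 51 / 50% | 97 / 47 / 47% | 99 / 59 / 59% |

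For a fixed f, equal controls are the most favourable pattern for beating both, so joint power stays below 95% in every row and column.

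**Step 4: another reading of the effect size.** If 0.06 is taken as the effect of each two-arm comparison, d = 2f = 0.505. Each comparison then has 89.9% power at 82 per arm (normal approximation), still below 95%.

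**The case against.** **The analysis plan may name the contrasts.** This is fair. The article is condensed, and contrasts and testing order are often left to the SAP. Their absence alone is not the point. But contrasts named elsewhere would not make the 95% in Sample size {14} apply to the objective in Objectives {7}. That mismatch lies within the article.

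**A reader might infer that the plan tests only the three-group F.** The text does not say so. It never uses the word omnibus, it speaks of ANCOVAs in the plural, and it does not rule out pairwise comparisons. The match on 2 degrees of freedom shows how the trial was sized, not which tests will be run.

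**A reader might infer that the type I error rate nearly doubles.** The documents do not support this. It would need success on either contrast to count and no preceding F test. The objective names both controls. If both must be significant, no alpha adjustment is needed. If the F test comes first, it holds the familywise error for three groups at about 4% under the global null.

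**The size depends on assumptions.** This also stands. The half-benefit pattern is not in the article, and with equal controls 88% at 82 per arm is respectable. The 75-per-arm column follows from applying the article's own 25% drop-out to 300. It is approximate, because the intention-to-treat analysis will use multiple imputation.

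**Conclusion.** The concern holds as a mismatch between the stated objective and the stated power. The 95% is the power of a three-group F test at partial eta squared 0.06. It is not the power to show Lenio superior to both controls, and a significant F would not by itself establish superiority over either.

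Under the most favourable pattern of means, joint power is about 88% at 82 per arm, 84% at 75 per arm and 94% with all 300 analysed. If the app delivers half of Lenio's benefit, the figures are about 50%, 47% and 59%. That the 246 comes from the three-group F test is firm, because of the variants tried only that test returns it. The size of the shortfall rests on the unstated pattern of means and is therefore given as a range. Nothing here shows an inflated error rate.

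**What to change.** 1. In Statistical methods {20a}, name two primary contrasts from the week-8 ANCOVA of DSF pain impairment: Lenio against waitlist, and Lenio against active control.
2. State that both must be significant at two-sided 0.05 to claim the full objective, in which case alpha need not be split. If a waitlist-only claim is also to be allowed, use a fixed sequence instead: waitlist first, then active control.
3. Report each contrast as an adjusted mean difference in DSF impairment points with a 95% confidence interval, beside partial eta squared.
4. In Sample size {14}, say that the 95% refers to the three-group F test, and give the contrast and joint power with the assumed pattern of means.

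The cost is wording only, with no new data, but the stated power becomes less favourable. The sample size can no longer be adjusted, because Current study status reports recruitment as complete. Data monitoring and auditing {21a; 23} says that first data were analysed for the funder in March 2022. The change must therefore be dated and disclosed as made after that look.
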